### Power analysis and sample size

Because the primary hypothesis concerns the investigation of the effect of the intervention in contrast to the waiting control group, power calculation is based solely on a repeated measure, within-between ANOVA. We strive for a statistical power of 99%; multiple-comparison problems are considered according to Cramer et al. [57]. A conservative estimate of *r* = 0.5 is used for the correlation between repeated measures of the same outcome to ensure enough power for outcomes with relatively low stability over time. Using the software G-Power, these specifications lead to a required sample size of 110 patients (2*55 per group intervention/waiting group) to detect an interaction when Cohen’s *f* for the interactions of 2*3 ANOVA is assumed to be moderate at 0.20. Based on our pilot groups, we assume that 10% of participants assigned to the intervention will not start intervention after assignment. Dropout rates from psychotherapy trials for BPD range between 22.3% and 28.2% [58]. In conclusion, we expect a dropout rate from baseline to follow-up assessment of 25%. Therefore, we assess *n* = 178 mothers with BPD for eligibility (*n* = 160 start the trial, *n* = 140 at post assessment, *n* = 120 at follow-up).

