### Methods: assignment of interventions

Sequence generation: Mothers with BPS are randomly assigned after inclusion to either control or intervention group with a 1:1 allocation as per a computer-generated randomization schedule (RedCap software) stratified by site.

Concealment mechanism: Allocation concealment will be ensured, as study staff will not release the randomization results until the participant has passed the baseline assessments. If randomization is run before baseline assessments, study staff running the randomization differ from those conducting baseline assessments. Otherwise, randomization is run after baseline assessments, and participants are informed via telephone.

When sufficient participants are randomized to the intervention group, personal data (name and phone number) are passed on to the group trainers who contact the group participants. Group trainers do not have access to participants’ study data (diagnosis, questionnaires) or IDs. All intervention material is passed on to the study staff and allocated to the respective ID.

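### Cohen's f = 0.20, which the power section calls moderate and pairs with 99% power, corresponds to a between-arm difference of about 0.85 SD; power for 0.5 SD is well below 99%

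*Protocol article*

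**What the plan says.** All the inputs but one are in the protocol article, section Power analysis and sample size.

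- Power: "We strive for a statistical power of 99" per cent.
- Test: the "power calculation is based solely on a repeated measure, within-between ANOVA", with two arms and three time points.
- Effect size: Cohen's f for the interaction in the 2*3 "ANOVA is assumed to be moderate at 0.20". No difference in SD or scale units is given, and no source for the value.
- Correlation: "0.5 is used for the correlation between repeated measures of the same outcome", described as a conservative choice.
- Alpha: no number. The text says only that "multiple-comparison problems are considered according to" a cited source.
- Result: a "required sample size of 110 patients (2*55 per group intervention/waiting group").
- Attrition: "we expect a dropout rate from baseline to follow-up assessment of 25" per cent, with 160 mothers starting, 140 at post assessment and 120 at follow-up.

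The section Methods: assignment of interventions gives a "1:1 allocation as per a computer-generated randomization schedule". The Objectives expect benefit at both later visits. The section Statistical analyses of intervention effects plans a linear mixed model with a time-by-intervention interaction.

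**The concern.** Cohen's f is usually judged by labels made for a one-way comparison of means, where 0.20 lies between small and medium. In a repeated-measures design with the correlation entered separately, the same f refers to interaction effects spread over six cells. The baseline cells carry no true arm difference, and each interaction effect is only half of a centred arm difference. A small-looking f can then stand for a large difference between arms.

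What is at stake is how the stated design property is understood. A reader who sees *moderate* beside 99% power will take the trial to be almost certain to detect a medium standardised difference in parenting or child abuse potential. If the label does not carry over, the trial is almost certain to detect only a much larger difference.

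**Working it through.** **1. Reproduce the 110.** Inputs: f = 0.20, r = 0.5, k = 2 arms, m = 3 visits, power 99%. With G*Power's default effect-size definition for this test and sphericity assumed:

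- noncentrality λ = f²·N·m/(1 − r) = 0.04 × 110 × 3/0.5 = 26.4
- df1 = (k − 1)(m − 1) = 2; df2 = (N − k)(m − 1) = 216

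Smallest even N for 99% power, by alpha:

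| alpha | N |
|---|---|
| 0.05 | 92 |
| 0.025 | 104 |
| 0.05/3 | 110 (power 0.991) |
| 0.0125 | 114 |
| 0.01 | 118 |

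So 110 is reproduced, and only for alpha between 0.0153 and 0.0173. The value 0.05/3 = 0.0167 fits but is an inference. The alternative SPSS-type effect-size option, which omits m/(1 − r), needs 272 patients at alpha 0.05 and 364 at alpha 0.0071. It cannot be the one used.

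**2. Convert f to SD units.** Under the definition that fits, f is the SD of the interaction effects over the six cells divided by the SD of a single measurement.

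*Sustained effect*, arm differences (0, d, d), as the Objectives suggest:
- centred differences: −2d/3, d/3, d/3
- interaction effects, ± half of these: d/3, d/6, d/6 in absolute value, in each arm
- sum of squares: 2 × (d²/9 + d²/36 + d²/36) = d²/3; divided by 6 cells: d²/18
- f = d/√18, so f = 0.20 gives d = 0.20 × 4.243 = **0.85 SD**

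*Linear build-up*, arm differences (0, d/2, d):
- sum of squares: 2 × (d²/16 + d²/16) = d²/4; divided by 6: d²/24
- f = d/√24, so f = 0.20 gives d = 0.20 × 4.899 = **0.98 SD** at month 9

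For any pattern with both later differences in the same direction (or one of them zero), the larger one lies between 0.85 and 0.98 SD. So 0.85 is the reading kindest to the protocol. This conversion does not depend on alpha.

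**3. Power for a sustained 0.5 SD**, that is f = 0.5/√18 = 0.118, at r = 0.5.

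- 110 complete cases: λ = (0.25/18) × 110 × 6 = 9.17
- 120 complete cases: λ = (0.25/18) × 120 × 6 = 10.0
- Planned mixed model with 160, 140 and 120 mothers at the three visits. Assume 1:1 arms, equal monotone loss, missing at random and compound symmetry. Each arm then has 60 mothers with three visits, 10 with two and 10 with baseline only. Let I be the information matrix per arm, δ = (0, 0.5, 0.5) and **1** the vector of ones. Then λ = ½[δ′Iδ − (δ′I**1**)²/(**1**′I**1**)] = ½(33.33 − 33.33²/113.33) = 11.76. As a check, the same formula with 55 complete mothers per arm gives ½(27.5 − 27.5²/82.5) = 9.17.

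| Data | alpha 0.05/3 | alpha 0.05 |
|---|---|---|
| 110 complete | 62% | 77% |
| 120 complete | 67% | 81% |
| Mixed model, 160/140/120 | about 76% | about 87% |

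Simulation of 20,000 trials with 110 complete cases agrees: 62.0% and 77.1% for 0.5 SD, and 99.0% at alpha 0.05/3 for 0.85 SD. With 110 complete cases at alpha 0.05/3, power is 80% for 0.59 SD and 90% for 0.67 SD. If the effect builds linearly to 0.5 SD at month 9, the 62% becomes 47%.

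**The case against.** **The sample size is right.** A reader might infer that 110 is a miscalculation. It is not: the stated inputs reproduce it, and the value 0.20 is printed, so the target can be recovered. The fault lies in what f = 0.20 is said to represent.

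**The 0.5 SD benchmark comes from outside.** The protocol names no standardised mean difference, means or SDs, and attaches its adjective to f. This stands in part: 0.5 SD is the conventional medium value, used here as a yardstick, and the conversion needs an assumed pattern. But the label then describes an effect that readers would call large once it is put in SD units. Only a sign-reversing pattern (0, d, −d) gives a smaller figure, 0.49 SD, and that contradicts the Objectives.

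**62% is not the power of the planned trial.** A reader might take it as such. That goes too far: it holds for 110 complete cases at an inferred alpha. The protocol plans for more mothers and for a model that uses partial data, hence the 76% or 87%. A higher correlation, which the word conservative allows, would also help. If r were 0.6, the mixed-model figures would be about 86% and 93%. With r = 0.7 and 110 complete cases, they would be 88% and 95%. A one-degree-of-freedom contrast of baseline with the mean of both later visits would have about 74% with 110 at alpha 0.05/3, but the section powers the two-degree-of-freedom interaction.

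**Nothing in the protocol says a null result will be read as excluding a moderate benefit.** That is so. Such a reading is a risk of the wording, not a stated plan, and the confidence interval should guard against it.

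**Conclusion.** The point holds as a misdescribed power property, not as an error in N. The design has 99% power (r = 0.5, alpha about 0.05/3, 110 complete cases) for a difference of about 0.85 SD sustained at both later visits, or 0.98 SD at month 9 if the effect builds linearly. It does not have 99% power for a difference usually called moderate. For a sustained 0.5 SD at the protocol's own correlation, power runs from 62% to about 87%, depending on alpha, on the number of mothers and on whether partial data are used.

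The assumptions are equal baseline means, equal SDs, compound symmetry and, for the mixed-model figures, data missing at random. The 0.85 SD figure does not depend on alpha; the power figures do. None of them allows for clustering within therapy groups, which would lower them. The documents do not support a claim that the trial is too small or that enrolment must change.

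**What to change.** In the section Power analysis and sample size:

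1. State the alpha actually used. The value 0.05/3 is only what 110 implies, and should not be written in unless the trial team confirms it.
2. Replace the description of f = 0.20 as moderate with the target in SD units and its pattern: f = 0.20 corresponds to a between-arm difference of 0.85 SD at both week 12 and month 9, with r = 0.5.
3. Tie the 99% to that difference.
4. Add the power for a sustained 0.5 SD at the planned numbers (160, 140, 120) and under the planned mixed model. That is about 76% if alpha is 0.05/3 and about 87% if it is 0.05, before any allowance for therapy-group clustering.

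Enrolment, outcomes and analysis stay as they are. The cost is a few reworded sentences and a less favourable stated figure.

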**Method:**

In a parallel-group, two-arm, randomized controlled trial, an initial *N* = 178 mothers diagnosed with BPD and their children aged 6 months to 6 years are assigned to either the parenting intervention or a waiting control group. If taking place, participants of both groups continue their regular treatment for BPD diagnosis (e.g., individual therapy, medication). The primary outcomes are changes in parenting from baseline (day 0) to post intervention (week 12) and follow-up (6 months after group intervention; month 9). The waiting control group can attend the group intervention at the end of all assessments. Participants allocated to the intervention group are expected to show improvement in their parenting and a reduction in child abuse potential. Maternal emotion regulation and mental distress are analyzed as secondary outcomes.

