#### Statistical analyses of intervention effects

Analyses follow the intent-to-treat framework. In particular, we will use linear mixed effects models [59] with their advantages in the handling of missing and longitudinal data to analyze of our primary outcome measures. The respective statistical models will include fixed effects for time, intervention and the interaction of time and intervention as well as random effects for the participants.

Differences in the effectiveness of the intervention across three sites will be investigated. The factor site will be included in all statistical analyses concerning the primary and secondary outcome measures if there are substantive differences.

Additionally, the effect of concomitant interventions will be investigated.

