### Methods: Data monitoring

Data monitoring is supervised by the Charité-BIH Clinical Study Center, which is independent of the study sponsor and has no competing interests. The trial will be stopped once the planned N is reached. Potential serious adverse events are monitored by the DSMC.

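### The figure 178 is the number assigned in the abstract but the number assessed for eligibility in the power section, and the step from 178 to 160 takes an intervention-arm loss from both arms.

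*Protocol article*

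**What the plan says.** All places are in the protocol article.

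- **Abstract, Method:** an initial 178 mothers "are assigned to either the parenting intervention or a waiting control group". Here 178 is a number randomised.
- **Power analysis and sample size:** "we assess *n* = 178 mothers with BPD for eligibility", followed by 160 who start the trial, 140 at post assessment and 120 at follow-up. The required sample is 110 (55 per arm) for 99% power at f = 0.20.
- **Same section, loss rates:** "we assume that 10% of participants assigned to the intervention will not start intervention after assignment", plus an expected 25% dropout between baseline and follow-up. No screen-failure rate is given.
- **Methods: assignment of interventions:** allocation is 1:1.
- **Methods: Data monitoring:** "The trial will be stopped once the planned N is reached". Which N this means is not said.
- **Statistical analyses of intervention effects:** "Analyses follow the intent-to-treat framework".

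**The concern.** Assessed for eligibility and assigned to an arm are different milestones. Under Study design, recruitment, and eligibility, a telephone screen and a diagnostic interview lie between them, and the listed exclusion criteria can remove mothers. One figure cannot serve for both unless nobody fails screening.

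The loss chain adds a second problem. Its first step carries an eligibility label, but the only rate that produces it describes an event after randomisation in one arm. So 178 was not derived as a screening number, and if it is the number randomised, the step removes about twice as many mothers as the stated rate implies.

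At stake are the recruitment target and the end of recruitment. The stop rule takes its meaning from whichever number is the planned one, and the completed trial will be judged against it.

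**Working it through.** **Inputs.** From Power analysis and sample size: 178, 160, 140, 120, required 110, 10% non-start, 25% dropout, f = 0.20, correlation 0.5, power 99%. From Methods: assignment of interventions: 1:1 allocation, so 178/2 = 89 per arm. Not stated, hence assumed: the numerical alpha (0.0125 to 0.05) and the screen-failure rate s (10%, 20%, 30%).

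**1. The plan's own chain.** With n × (1 − loss):

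- 178 × 0.90 = 160.2, stated as 160
- 160 × 0.75 = 120, as stated

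The multiplication is right. It reproduces only if the 10% is taken from all 178.

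**2. The required 110.** I used the repeated-measures within-between interaction test, with noncentrality f² × N × m / (1 − ρ), m = 3 time points, two groups, ρ = 0.5, and degrees of freedom 2 and 2(N − 2). At an assumed alpha of 0.05/3, 99% power needs N = 110, the plan's figure. Alpha 0.05 gives 92, 0.025 gives 104 and 0.0125 gives 114.

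**3. The 10% where the text puts it.** Ten per cent of 89 is 8.9, about 9 mothers, leaving about 169 of 178. The plan removes 178 − 160 = 18. If these were all intervention non-starters, they would be 18/89 = 20% of that arm, twice the stated rate.

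**4. If 178 is the randomised and baseline number.**

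- 25% loss from baseline: 178 × 0.75 = 133.5, about 134
- Intervention non-starters also lost: (178 − 8.9) × 0.75 = 126.8, about 127

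Both exceed 110 and the plan's 120. At f = 0.20 and alpha from 0.0125 to 0.05, power is at least 0.995 at 127 and at 134.

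**5. If 160 is the randomised number.**

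- 25% loss: 160 × 0.75 = 120
- Intervention non-starters also lost (10% of 80 = 8): 152 × 0.75 = 114

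Both exceed 110.

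**6. If 178 is only the number assessed.** Follow-up count = 178 × (1 − s) × 0.75, with s assumed. Power is at f = 0.20.

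| s | randomised | at follow-up | power, alpha 0.05 | power, alpha 0.05/3 | power, alpha 0.0125 |
|---|---|---|---|---|---|
| 10% | 160 | 120 | 0.999 | 0.995 | 0.994 |
| 20% | 142 | 107 | 0.997 | 0.989 | 0.986 |
| 30% | 125 | 93 | 0.992 | 0.974 | 0.967 |

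The count falls below 110 when s exceeds 1 − 110/133.5 = 17.6%.

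**7. Sensitivity to dilution.** Suppose that f = 0.20 refers to mothers who start, that 10% of the intervention arm gains nothing, and that alpha is 0.05/3. Then f becomes 0.20 × 0.9 = 0.18, and power is 0.980 at 120 and 0.990 at 134. The plan states none of these three assumptions.

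**The case against.** The strongest reply is that this is loose labelling with little consequence. The chain multiplies correctly, and 160 to 120 is exactly 25%. The section on assignment of interventions allows randomisation before the baseline assessments, so 178 could be assigned, 160 could form the baseline and 120 could reach follow-up. On that reading the 25% is used as defined. The fall of 58/178 = 32.6% from 178 to 120 then combines two separately stated losses and does not contradict the 25%. This stands, and it is why the figure of 134 is conditional on 178 being the baseline number. It does not rescue the 10%, which is still taken from both arms at a step labelled eligibility.

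A reader might infer that the trial will miss its required 110. The documents do not support this as a fact. It needs 178 to be the number assessed and an unstated screen-failure rate above about 17.6%; at 10% the count is 120, as planned.

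A reader might also infer that non-starters are dropped from the analysis, which would break the randomised comparison. The documents do not say so. The power section projects attrition. The analysis section states intention-to-treat, the drop-out criteria do not list failure to start the intervention, and mothers who miss the post assessment are still contacted for follow-up. Budgeting for the loss of non-starters' data is cautious planning, not an exclusion rule.

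**Conclusion.** The concern holds in a limited form. The abstract and the power section give 178 incompatible meanings, and the step to 160 applies to both arms a rate defined for one. The undefined planned N in the stop rule follows from the same ambiguity and is not a separate fault.

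The size depends on which meaning is intended. With 178 randomised at baseline, about 127 to 134 remain against 110 required, so the error is conservative. With 178 only assessed, an assumed screen failure of 10%, 20% or 30% leaves about 120, 107 or 93. Even 93 keeps power at 0.967 or more at f = 0.20 over the assumed alphas, so the shortfall is measured against a very high 99% target. The documents do not settle whether 178 or 160 is to be randomised. This should be fixed, but it does not put the trial's validity in doubt.

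**What to change.** The sponsor should:

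1. State one number to be randomised, 178 or 160, and use it in both the abstract and the power section.
2. Give the number to be screened separately, with its assumed screen-failure rate.
3. Apply the 10% non-start rate to the intervention arm only, and keep non-starters in the intention-to-treat count.
4. Restate the expected numbers at post assessment and follow-up, and the resulting power with the alpha used.
5. Define the planned N under Methods: Data monitoring as the number randomised.
6. Show any power loss from dilution only as a sensitivity figure with its assumptions.

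The cost is a few sentences and one recomputed power figure. On either candidate number, the stated rates leave at least 110 at follow-up (127 to 134 from 178; 114 to 120 from 160), so the correction calls for no mothers beyond the number chosen. If 178 was meant as the number assessed, more mothers may have to be screened.

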### Methods: assignment of interventions

Sequence generation: Mothers with BPS are randomly assigned after inclusion to either control or intervention group with a 1:1 allocation as per a computer-generated randomization schedule (RedCap software) stratified by site.

Concealment mechanism: Allocation concealment will be ensured, as study staff will not release the randomization results until the participant has passed the baseline assessments. If randomization is run before baseline assessments, study staff running the randomization differ from those conducting baseline assessments. Otherwise, randomization is run after baseline assessments, and participants are informed via telephone.

When sufficient participants are randomized to the intervention group, personal data (name and phone number) are passed on to the group trainers who contact the group participants. Group trainers do not have access to participants’ study data (diagnosis, questionnaires) or IDs. All intervention material is passed on to the study staff and allocated to the respective ID.

### Methods: data collection, management, and analysis

#### Preliminary statistical analyses

Descriptive statistics, correlations of variables, drop-out analyses, and randomization tests are analyzed first.

#### Statistical analyses of intervention effects

Analyses follow the intent-to-treat framework. In particular, we will use linear mixed effects models [59] with their advantages in the handling of missing and longitudinal data to analyze of our primary outcome measures. The respective statistical models will include fixed effects for time, intervention and the interaction of time and intervention as well as random effects for the participants.

Differences in the effectiveness of the intervention across three sites will be investigated. The factor site will be included in all statistical analyses concerning the primary and secondary outcome measures if there are substantive differences.

Additionally, the effect of concomitant interventions will be investigated.

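### The planned mixed model is valid but estimates a free day-0 difference between the arms; a common baseline mean would cut the variance of the treatment contrasts by about 20 to 25% at the plan's own correlation

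*Protocol article*

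**What the plan says.** The section on statistical analyses of intervention effects specifies a linear mixed model, under intention to treat, with "fixed effects for time, intervention and the interaction of time and intervention" "as well as random effects for the participants". Primary outcomes are measured at day 0, week 12 and month 9. The abstract defines the target as change: "The primary outcomes are changes in parenting from baseline (day 0) to post intervention (week 12) and follow-up".

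The sample size section plans for the same quantity. There the "power calculation is based solely on a repeated measure, within-between ANOVA", and the effect to be detected is the interaction in a 2 x 3 layout. A value of 0.5 "is used for the correlation between repeated measures of the same outcome", and the plan calls this value conservative.

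The section on assignment of interventions describes 1:1 random assignment stratified by site, with the result withheld until baseline is complete. The article does not mention a common baseline mean or the day-0 score as a covariate.

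**The concern.** With day 0 among the outcomes and an intervention main effect in the model, the day-0 arm difference is a free parameter. Each time-by-intervention term is then a later arm difference minus the day-0 arm difference. Randomisation, with the result concealed until baseline is done, makes the expected day-0 difference zero, so the model spends information on a quantity already known by design.

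Two things follow. The contrast has a larger variance than it needs, most of all for outcomes with low stability over time, which is the case the sample size section says it wants to protect. And in any one trial a chance imbalance at day 0 passes into the estimate through regression to the mean. Both recur on each outcome analysed this way.

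**Working it through.** **Inputs.** From the sample size section: correlation r = 0.5, Cohen's f = 0.20, power 99%, N = 110 (55 per arm), and expected numbers 160, 140 and 120 at the three times. From the analysis section: the fixed effects above and participant random effects.

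**Assumptions.** A random intercept, hence compound symmetry; unit outcome SD; individual assignment as in the section on assignment of interventions (the trial design section uses the word clustered); dropout monotone and equal by arm. No alpha is given in figures.

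**1. The plan's own figure.** For the within-between interaction in G*Power, lambda = f² x N x 3 / (1 - r), with 2 and 2(N - 2) degrees of freedom. At N = 110, lambda = 0.04 x 110 x 3 / 0.5 = 26.4.
- Alpha 0.05: N = 92 suffices for 99% power.
- Alpha 0.05/3 = 0.0167: N = 110 is needed, with power 99.1%.

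The stated 110 is thus reproduced at an assumed alpha of 0.0167, and it belongs to the free-baseline interaction test.

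**2. Variance of one arm contrast, complete data.**
- Free baseline (change score): factor 2(1 - r) = 1.00.
- Common baseline mean: factor 1 - r² = 0.75.
- Share saved: 1 - (1 - r²) / [2(1 - r)] = (1 - r)/2.

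| r | share saved |
|---|---|
| 0.3 | 35% |
| 0.5 | 25% |
| 0.7 | 15% |
| 0.8 | 10% |

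At r = 0.5 the standard error falls by 1 - √0.75 = 13%. For a single contrast, 110 mothers would do the work of 110 / 0.75 = about 147.

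**3. With the planned attrition.** Generalised least squares with 160, 140 and 120 mothers at r = 0.5:

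| visit | variance, free | variance, common baseline | ratio |
|---|---|---|---|
| week 12 | 0.0277 | 0.0214 | 0.774 |
| month 9 | 0.0309 | 0.0246 | 0.797 |

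The saving is 23% and 20%, equivalent to 1/0.774 = 1.29 and 1/0.797 = 1.25 times as many mothers.

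**4. Chance imbalance.** Given a day-0 imbalance D, the change-score estimate shifts by -(1 - r)D. With 55 per arm, one standard error of D is √(2/55) = 0.19 SD, so at r = 0.5 an ordinary imbalance moves the estimate by about 0.10 SD.

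**5. Power at the planned effect.** For the two-degree-of-freedom interaction test at f = 0.20, N = 110 and assumed alpha 0.0167, power rises from 99.1% to between 99.6% (effect at one visit only) and 99.98% (sustained effect). In the convention that reproduces N = 110, f = 0.20 corresponds to about 0.85 SD between arms, whether sustained or at one visit only. A t-test at one visit with 0.85 SD and 55 per arm goes from 99.3% to 99.9% (alpha 0.05), or from 97.7% to 99.6% (alpha 0.0167).

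**6. Power at a smaller effect, for illustration only.** An assumed 0.5 SD at one visit, with 55 per arm and alpha 0.05, gives 74% with variance 1.00 and 85% with variance 0.75. The 0.5 SD is not a figure from the plan.

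**The case against.** Time by intervention in a mixed model is a standard analysis. It is unbiased over randomisation, controls type I error, and agrees with the article's definition of the outcome as change and with its sample size method. All of that stands. A reader might infer from the variance figures that the analysis is biased or that the trial is underpowered for its stated effect. The documents support neither: the imbalance shift is conditional on the imbalance that happens to arise, and N = 110 was computed for this same test.

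A reader might also take the rise from 74% to 85% as the power the plan loses. It is not, because it rests on an effect well below the planned one and on an alpha the article does not state. Nor does the full quarter apply everywhere. It needs complete data and r = 0.5, which the plan introduces as "A conservative estimate of" the correlation; more stable outcomes lose less. On the two-degree-of-freedom test, an effect at one visit only costs 11% of the noncentrality, against 33% for a sustained effect.

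It can be said that a condensed article leaves model detail to the analysis plan. This holds for covariance structure and covariates, but the fixed effects are stated here, and they include the intervention main effect.

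Finally, randomisation may be run before the baseline assessment. The equal-baseline premise then rests on concealment of the result. The article provides for that concealment, with different staff running the randomisation and the assessments, so the premise holds, though only in expectation and only if concealment is kept.

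**Conclusion.** The point holds as a matter of efficiency. Under compound symmetry and r = 0.5, the stated model gives each arm contrast a variance that a common baseline mean would cut by 25% with complete data, and by 23% at week 12 and 20% at month 9 with the planned attrition. With r between 0.7 and 0.8 and complete data the cut is 10 to 15%. The change also removes the shift of about -(1 - r) times any chance imbalance at day 0.

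It is not a type I error problem or an unconditional bias, and it does not undermine the planned 99% power. At f = 0.20 the power gain is small. The benefit is narrower intervals on every outcome analysed this way, and useful power if the true effect is smaller than planned. Because the remedy needs no data beyond those already collected, it is worth making before analysis.

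**What to change.** Keep day 0 as an outcome, drop the intervention main effect at day 0 so that both arms share one baseline mean, and estimate intervention effects at week 12 and at month 9. Mothers with only a baseline value still contribute.

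Alternatively, use week 12 and month 9 as the outcomes, with the day-0 score and its interaction with time as covariates. This is nearly the same analysis, except that mothers with only a baseline value do not contribute.

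State that the common baseline mean relies on the allocation result being concealed until baseline is complete. The cost is a change of model wording: day-0 scores on the primary and secondary questionnaires are already scheduled, and no new visits or participants are needed.
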